#### Secondary outcomes

Secondary outcomes will include the following:

Mean proportion of adequately reported C-short items in published articles considering each item separately.Difference in mean proportion of adequately reported C-short items in published articles considering each sub-item (see ‘Assessment of outcomes’) as a separate item.Time from assigning an editor to the first decision (as communicated to the author after the first round of peer review).Proportion of manuscripts rejected after the first round of peer review.Proportion of manuscripts that will be published in the journal under study.

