#### Populations of analysis

The main population for analysis will be all manuscripts randomised and accepted for publication in the participating journals. In contrast to RCTs conducted with patients, where losses to follow-up need to be carefully considered (eg, multiple imputation of missing data), we are only interested in the reporting adherence of RCTs that are published. As such, we will exclude randomised manuscripts that were not published from the main analysis. All outcomes will be calculated based on the main population. The secondary outcome ‘Time to the first decision’ will additionally be calculated considering all randomised manuscripts (including the ones which were not published). For all analyses a p-value of 0.05 (5% significance level) will be used to indicate statistical significance. Exact p-values will be presented up to three decimal places. We anticipate there will be no missing data in this study, neither at the individual C-short items, nor at the manuscript level. This is due to the study design, which will include only the randomised manuscripts that are accepted for publication. We will analyse if the rate of manuscripts rejected after the first round of peer review and if the proportion of manuscripts that will be published differentiate among the two study arms (both secondary results).

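### The population rule puts the rejection and publication proportions on accepted manuscripts only, which fixes them at about 0% and 100% in both arms and contradicts the promised comparison

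*Protocol article*

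**What the plan says.** All of the following is in the protocol article.

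- **Main population** (Populations of analysis): "The main population for analysis will be all manuscripts randomised and accepted for publication in the participating journals". The reason given is that interest lies in reporting adherence in published trials, and so "we will exclude randomised manuscripts that were not published from the main analysis".
- **Scope of that population** (same section): "All outcomes will be calculated based on the main population".
- **The one stated extension** (same section): "The secondary outcome ‘Time to the first decision’ will additionally be calculated considering all randomised manuscripts (including the ones which were not published").
- **Closing commitment** (same section): "We will analyse if the rate of manuscripts rejected after the first round of peer review", and likewise the proportion published, differs between the arms. Both are labelled secondary results. No other population or denominator is named for them.
- **Secondary outcomes** list both proportions, the second as "Proportion of manuscripts that will be published in the journal under study".
- **Analysis of secondary endpoints** promises mean differences with 95% CIs for the secondary outcomes.
- **Sample size** continues randomisation until each arm has 83 published articles, allows three further months for articles in production, and excludes anything published later.

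**The concern.** A manuscript enters the main population only if it was accepted. Within that set, being published is almost a condition of entry and being rejected after round one is almost excluded. Calculating the two proportions there gives a difference that says nothing about the intervention.

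This matters because the primary analysis conditions on publication, which happens after randomisation. The intervention asks reviewers to look for reporting gaps, so it could plausibly change which manuscripts are rejected. Comparing rejection and publication across everything randomised is the direct check on whether that selection differs by arm. The trial characteristics in Table 2 help only partly, because they are assessed on published articles. With time to first decision, the two proportions are also the listed outcomes that would show an unwanted effect on the editorial process.

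A smaller related point concerns time to first decision. Its main-population result leaves out manuscripts rejected at that decision, and the all-randomised result is labelled as an addition.

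**Working it through.** **1. The plan's own figure.** Inputs from Sample size, second scenario: 71% against 82% (difference 0.11), SD 0.25, two-sided 5%, power 80%. The normal approximation gives n = 2 × (1.96 + 0.8416)² × 0.25² / 0.11² = 81.1, so 82 per arm. The t-test solution is 82.05, so 83 per arm and 166 in total, as stated. Power at 83 per arm is 0.805. The figure reproduces and does not depend on the point below.

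**2. The rule applied as written.** Take 83 accepted and published manuscripts per arm. This is the minimum; one arm may exceed it.

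| Outcome in main population | Intervention | Control | Difference | SE |
|---|---|---|---|---|
| Rejected after round one | 0/83 | 0/83 | 0 | 0 |
| Published | 83/83 | 83/83 | 0 | 0 |

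The SE is √(p(1−p)/83 + p(1−p)/83), which is 0 at p = 0 or p = 1. Small departures are possible, for example a rejection reversed on appeal, or an acceptance not yet published. They would not make the comparison informative.

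**3. The sentences side by side.** The general sentence assigns every outcome to the main population. The next sentence names one outcome to be calculated additionally on all randomised manuscripts, so the two proportions stay under the general rule. The closing sentence then commits to comparing them between arms. The rule and the commitment cannot both be carried out in a meaningful way.

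**4. What all randomised manuscripts would give.** The article states no publication rate, so p below is an assumption shown over a range. Randomised per arm: N = 83/p, rounded up. Half-width: 1.96 × √(2p(1−p)/N), with p equal in both arms. The last column is the fall in the publication proportion detectable with 80% power at two-sided 5%.

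| Assumed p | N per arm | 95% CI half-width (points) | Detectable fall (points) |
|---|---|---|---|
| 30% | 277 | 7.6 | 10 |
| 40% | 208 | 9.4 | 13 |
| 50% | 166 | 10.8 | 15 |
| 60% | 139 | 11.5 | 17 |
| 70% | 119 | 11.6 | 18 |

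For example, at 30%: 1.96 × √(2 × 0.3 × 0.7 / 277) = 1.96 × 0.0389 = 0.076. These are approximations: they treat N as fixed, whereas recruitment stops on the count of published articles.

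**The case against.** The strongest reply is that the intent is evident. The closing sentence commits to the comparison. Table 2 places the rejection outcome at the first decision, before publication. Assessment of outcomes takes both proportions from the editorial system or the journal, not from published articles. The stated reason for the published-only restriction is relevant only to reporting adherence. A sensible analyst would probably use all randomised manuscripts. This stands as an account of intent, and it makes a table of 0/83 against 0/83 unlikely in practice. It does not remove the contradiction: the text does state a population for these outcomes, and it is one that cannot answer the question.

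The original approved protocol, supplied as an appendix and not shown here, may name the denominator. That would not reconcile the sentences in the article.

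A reader might infer three stronger things that the documents do not support:

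- **That no outcome is analysed beyond published manuscripts.** Time to first decision is also to be calculated on all randomised manuscripts.
- **That time to first decision is degenerate too.** It varies among published manuscripts. The only issue there is which of two planned analyses is called the main one.
- **That the comparison has become impossible.** The data are collected either way, so nothing is lost if the rule is corrected before analysis.

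It is also fair to say that moving to all randomised manuscripts is not free of difficulty. When recruitment stops, some manuscripts may still be under review or in production.

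**Conclusion.** The point holds as a contradiction within Populations of analysis, limited to the denominator of two secondary proportions. Read literally, the rule makes both uninformative: about 0% and 100% in each arm, with no usable difference, interval or test. That follows from the definition of the set and needs no numerical assumption.

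The primary outcome, its population and the sample size are untouched. What is at risk is the check on whether publication, on which the primary analysis conditions, differs by arm.

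On all randomised manuscripts the comparison becomes informative but only moderately precise: a half-width of roughly 8 to 12 percentage points for the difference in publication. That range rests on an assumed publication rate of 30% to 70%, similar in both arms, and on 83 published articles per arm.

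**What to change.** Replace the sentence on scope with a rule by outcome:

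- C-short adherence outcomes (overall, by item and by sub-item) are calculated on the main population.
- The proportion rejected after round one and the proportion published are calculated on all randomised manuscripts, by allocated arm.
- Time to first decision has all randomised manuscripts as its main analysis, with the published-only result as supplementary.

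Add a sentence on how manuscripts without a decision when follow-up closes are counted, and the same for those published after the three-month cut-off. One workable rule is to define the second proportion as published by the cut-off, count later publications as not published by then, and report the number still undecided in each arm. Whichever rule is chosen, it should be fixed before the data are compared.

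The cost is a few sentences. The editorial data are already to be extracted, or provided by the journals, under Assessment of outcomes and Data management and confidentiality, and recruitment does not change. The small downside is that some manuscripts will be undecided at the cut-off, so the two proportions will carry some incomplete follow-up that the published-only set does not have.

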#### Analysis of primary endpoint

The effect of the intervention will be estimated as the mean difference in the proportion of C-short items adequately reported between the study arms. If the data on the primary outcome are normally distributed, groups will be compared using an unpaired Student’s t-test. If the data are not normally distributed, comparisons will be performed using a non-parametric equivalent test (ie, Wilcoxon-Mann-Whitney test).

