### Participant timeline

The overview of the study schedule, including enrolment, intervention and assessments, is presented in table 2.

**Table 2 T2:** Study schedule

	Enrolment	Allocation and intervention	Intervention	Post-intervention	
Time point	Studies which are sent out for peer review	After first peer reviewer accepts invitation	Whenever an additional peer reviewer accepts invitation	First decision by journal	Published manuscripts
Eligibility screen	X				
Allocation		X			
Intervention:					
C-short + usual care		X	X		
Usual care		X	X		
Assessment of trial characteristics:					
Funding source					X
Study centres (single centre or multicentre)					X
Sample size					X
Study design (eg, parallel arm, crossover)					X
Hypothesis (eg, superiority, non-inferiority)					X
Medical field					X
Intervention tested					X
Number of trial arms					X
Number of peer reviewers					X
Journal which published the manuscript					X
Number of journals requesting CONSORT adherence (submission of checklist mandatory)					X
Assessment of outcomes:					
Time from assigning an academic editor until the first decision				X	
Proportion of manuscripts directly rejected after the first round of peer review				X	
Proportion of manuscripts that will be published in the journal under study					X
Adherence to CONSORT items and sub-items					X

CONSORT, CONsolidated Standards of Reporting Trials.

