Two authors of this protocol, working for *PLOS ONE* (IP and AC), one of the participating journals, pointed out that 3 out of the 10 assessed items (ie, item ‘Registration’, ‘Protocol’ and ‘Funding’) should always be implemented in submissions to their journal given their policy requirements for clinical trials. Assuming that this journal will recruit a high proportion of manuscripts, and that also other journals might update their templates, we increased the sample size in a second scenario, in which all these three items would have an overall adherence of 90% in the control arm (table 3). This would entail an overall baseline adherence with the 10 C-short items of 71%. Based on a two sided t-test, a sample size of 166 (83 per treatment arm) will have a power of 80% to find a 15% relative increase (71% adherence in control group; 82% adherence in intervention group; SD=0.25; a type 1 error at 5%).

Since the final sample size will be based on the number of articles published, rather than on the number of manuscripts randomised, eligible manuscripts will be randomised until 83 articles are published in each arm (resulting in no less than 166 articles), to avoid loss of power due to potential imbalance between arms. Recruitment will be stopped as soon as both arms reach the sample size of 83. After recruitment has stopped we will wait 3 months so that manuscripts, which are still in production, can be published. Manuscripts which are published after the 3-month period will be excluded.

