### Randomisation and blinding

Manuscripts meeting the eligibility criteria and sent out for external peer review by the journals will be randomised into one of the two groups (allocation 1:1). The randomisation list will be created by the Study-Randomizer system^34^ using random block sizes between 2 and 8 and stratified by journal. As soon as the first peer reviewer accepts the invitation, the manuscript will be included and randomised to one of the two study arms. One of the investigators (BS) will log onto the Study-Randomizer system^34^ and enter the study identification number (ID; provided by the journal), the study title and the journal the study was submitted to. Subsequently, all additional peer reviewers accepting the invitation to review the same manuscript will receive the same group assignment as the first peer reviewer.

Authors will be blinded to the intervention. Editors will not be actively informed about the randomisation (possible exception listed under ‘Interventions’). To avoid potential bias, peer reviewers and manuscript authors will not be informed of the study hypothesis, design and intervention.

Outcomes will be assessed in duplicate (see ‘Assessment of outcomes’). At least one outcome assessor will be blinded. Due to restricted resources the investigator conducting the randomisation (BS) might be involved in the data extraction from published manuscripts.

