#### Pre-specified subgroup analysis

No formal subgroup comparative analysis is planned for the primary or secondary outcomes. However, the effect of the intervention on the primary outcome within subgroups will be presented using forest plots to visually examine whether it may differ according to some variables such as: (i) journals that actively implement the CONSORT Statement (defined as requiring authors to submit a completed CONSORT checklist alongside their manuscript) versus journals that are not actively implementing the CONSORT statement, (ii) sample size of included RCTs (n<100 vs n≥100) and (iii) impact factor (<5, 5.1–10;>10) as there is evidence that higher impact factor and higher sample size are associated with higher adherence to reporting guidelines.^35^ Subgroup analysis at the journal level will only be conducted when sufficient journals are in each group so that no results of individual journals are revealed. All analyses will be exploratory, with the aim of supporting new hypothesis generation, rather than being conclusive.

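### The primary comparison is unadjusted although the plan already collects a cited predictor of adherence, RCT sample size: a modest, avoidable loss of precision, not an error

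*Protocol article*

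**What the plan says.** Analysis of primary endpoint, in the Protocol article, fixes both the estimator and the test. The estimator is a raw contrast: "The effect of the intervention will be estimated as the mean difference in the proportion of C-short items adequately reported between the study arms". For the test, it says "If the data on the primary outcome are normally distributed, groups will be compared using an unpaired" t-test, with the Wilcoxon-Mann-Whitney test as the alternative. Neither takes a covariate.

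Three other places bear on this:

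- **Table 2 (Participant timeline).** Under "Assessment of trial characteristics", the sample size of each RCT is listed for collection from the published article.
- **Pre-specified subgroup analysis.** The article states that "there is evidence that higher impact factor and higher sample size are associated with higher adherence to reporting guidelines". RCT size is then used only to split an exploratory forest plot at 100 participants.
- **Randomisation and blinding.** The allocation list is built "using random block sizes between 2 and 8 and stratified by journal". Nothing in the design balances RCT size within a journal.

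The Discussion adds that no adjustment for clustering by journal is intended, on the ground that contamination between arms is unlikely.

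**The concern.** The plan names a predictor of its own primary outcome, collects it for other purposes, and leaves it out of the one analysis where it would help most. Any outcome variation that RCT size explains therefore stays in the error term, and the confidence interval is wider than it need be. The final target gives only about 80% power, so even a small gain is worth having when it costs nothing.

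A second strand concerns balance. The main analysis set is the published subset of the randomised manuscripts. The arms may differ in RCT size there, by chance or because publication depends on arm, and an unadjusted difference carries that imbalance with it.

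The covariate is suitable in principle. The number of participants in an RCT is fixed before its manuscript reaches the journal, so a reviewer reminder cannot alter it, even though it is read from the article afterwards.

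**Working it through.** **Inputs from the Protocol article (Sample size, scenario 2).** Control 0.71, intervention 0.82, so δ = 0.11. SD σ = 0.25; two-sided α = 0.05; n = 83 per arm. The stated result is that "a sample size of 166 (83 per treatment arm) will have a power of 80% to find a 15% relative increase".

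**Step 1: reproduce the plan's figure.** The standardised effect is 0.11/0.25 = 0.44. Solving the two-sample t-test for 80% power gives 82.05 per arm, which rounds up to 83. At 83 per arm, SE = 0.25 × √(2/83) = 0.0388, the noncentrality is 0.11/0.0388 = 2.835, and power is 80.5%. The stated sample size is correct for the unadjusted test.

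**Step 2: add RCT size as a covariate.** The article gives the direction of the association but not its strength. R², the share of outcome variance explained by RCT size, is therefore an assumption, taken here from 2% to 10%. The formulas are:

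- residual SD = 0.25 × √(1 − R²)
- SE = residual SD × √(2/83)
- noncentrality = 0.11/SE
- power from the noncentral t distribution with 164 degrees of freedom unadjusted, 163 adjusted
- equivalent n per arm = 83/(1 − R²)

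| R² | Residual SD | SE | Noncentrality | Power | 95% CI half-width | Equivalent n per arm |
|---|---|---|---|---|---|---|
| 0 | 0.2500 | 0.0388 | 2.835 | 80.5% | 0.0766 | 83 |
| 2% | 0.2475 | 0.0384 | 2.863 | 81.2% | 0.0759 | 84.7 |
| 5% | 0.2437 | 0.0378 | 2.908 | 82.4% | 0.0747 | 87.4 |
| 10% | 0.2372 | 0.0368 | 2.988 | 84.4% | 0.0727 | 92.2 |

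The interval narrows by 1 − √(1 − R²), that is by 1.0%, 2.5% and 5.1%. The gain equals about 2, 4 or 9 further published articles per arm.

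**Step 3: size of a chance imbalance.** Assume that half of the RCTs have at least 100 participants and that mean adherence differs by D across that cut. The between-arm difference in the share of large RCTs has SD √(2 × 0.25/83) = 0.078. A 1.96-SD imbalance is 0.152, and it moves the raw difference by 0.152 × D. For D = 0.10 the shift is 0.015, and for D = 0.20 it is 0.030, against a target effect of 0.11. In terms of variance explained, R² = D² × 0.25/0.25², so D = 0.10 corresponds to 4%. D = 0.20 corresponds to 16%, which lies above the range in Step 2 and should be read as an outer case.

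**The case against.** The case for leaving the plan alone is substantial.

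- **The unadjusted test is sound.** It keeps its type I error, it matches the test used for the sample size, and it delivers the stated power. This stands. A reader might infer that omitting RCT size biases the estimate or makes the test invalid. The documents do not support that: chance imbalance is already reflected in the unadjusted confidence interval.
- **The gain is small and assumed.** At most 3.9 power points are at stake over the range shown (84.4 − 80.5), and no source for R² is visible. This stands too, and it limits how strongly the point can be put.
- **Journal may carry part of the effect.** Impact factor and RCT size are cited together. If larger RCTs go to higher-impact journals, stratification by journal already balances part of the RCT-size effect. With journal in the model, only the within-journal association adds precision. The documents say nothing about its strength, so the table may overstate the increment.
- **Selection into publication is a different problem.** A reader might infer that adjustment repairs the restriction to published articles. It does not. It removes only imbalance on this one measured predictor. No passage suggests that the arm changes publication according to RCT size, and the plan already compares rejection and publication between arms.
- **Adjusted analyses may be left to the analysis plan.** That is true of supportive analyses. Here, however, the article itself fixes the primary estimator and test, so the point concerns a stated choice.

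None of this shows a real cost to adjusting, and none removes the gain in precision.

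**Conclusion.** The point holds as an inexpensive improvement to a valid analysis. The Protocol article fixes an unadjusted primary comparison while collecting a pre-randomisation characteristic that it cites as associated with the outcome.

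Under an assumed R² of 2% to 10%, power at 83 per arm would rise from 80.5% to between 81.2% and 84.4%, and the confidence interval would narrow by 1% to 5%. If the within-journal association is weaker than that, the gain is smaller still. Larger gains would need an association that nothing in the documents supports.

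Adjustment would also remove imbalance on RCT size, whatever its source, but not selection on other factors. The direction of the point is secure; its size rests wholly on the assumed R².

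**What to change.** In Analysis of primary endpoint, prespecify a linear model of the C-short proportion with these terms:

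- study arm;
- log RCT sample size, defined as the number of individual participants and counted the same way for all designs, including cluster and crossover trials, with a stated fallback if an article does not report it;
- journal, the stratification factor, with very small journals pooled by a rule set in advance.

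Use robust standard errors. Take the primary mean difference, 95% confidence interval and p-value from this model, and report the unadjusted difference as supportive. The target of estimation stays the mean difference in proportion. Amend the Discussion's statement on clustering by journal so that it agrees with journal being in the model.

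The cost is a few sentences of analysis wording. RCT size and journal are both already listed in Table 2, and the sample size does not change. The change should be made before outcome data by arm are seen, since a covariate added later would look selective.

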### Outcomes

#### Primary outcome

The primary outcome of this study will be the difference in the mean proportion of adequately reported C-short items in published articles between the two groups.

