#### Assessment of outcomes

The outcomes will be assessed independently by two (blinded or at least partially blinded; see ‘blinding’) outcome assessors with expertise in the design and reporting of clinical trials. Any disagreement will be resolved by consensus or if necessary by consulting a third assessor. To ensure consistency between reviewers, we will first pilot the data extraction form; any disparities in the interpretation will be discussed and the data extraction form will be modified accordingly.

Adequate reporting of items will be assessed in duplicate from published full-text publications following the same instructions as provided by the CONSORT C-short checklist.^11^ The following checklist items have, due to their complexity, sub-items which will be extracted separately. The sub-items are highlighted in the short explanation of the intervention (see table 1 and online supplementary appendix 1):

Outcomes (item 6a): (i) define primary outcome, (ii) how it was measured, (iii) at what time point and (iv) the analysis metric (eg, change from baseline, final value).Sample size (item 7a): (i) the estimated outcomes in each group, (ii) the α (type I) error level, (iii) the statistical power (or the β (type II) error level), (iv) for continuous outcomes, the SD of the measurements.Blinding (item 11a): Is the blinding status clear for the following persons: (i) healthcare provider, (ii) patients and (iii) outcome assessors.Funding (item 25): (i) the funding source, and (ii) the role of funder in the design, conduct, analysis and reporting.

All items will be judged as either ‘yes’ meaning adequately reported, ‘no’ meaning not adequately reported or not reported at all, or ‘NA’ meaning that this sub-item is not applicable for this RCT. Items with different sub-items will only be judged as adequately reported if all relevant sub-items were adequately reported.

The outcomes ‘time from assigning an editor to the first decision’, ‘proportion of manuscripts rejected after the first round of peer-review’ and ‘proportion of manuscripts that will be published in the journal under study’ will be extracted directly from the journal’s editorial system or provided by the journal.

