### Data analysis

All quantitative variables will be described using means and SD, or medians and interquartile ranges in case severe departures from a normal distribution are identified. Data distributions will be inspected visually (ie, by histograms) instead of performing formal statistical tests for normality. Categorical variables will be described using frequencies and percentages. For the primary and secondary outcomes, we will estimate the mean difference between the two groups and report them with respective 95% CI. No interim analysis will be conducted.

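### The primary p-value comes from a t-test or a Wilcoxon test depending on a look at the histogram, and the likelier of the two does not test the mean difference that the trial defines and reports

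*Protocol article*

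**What the plan says.** All references are to the Protocol article.

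- **Primary outcome** defines the target as "the difference in the mean proportion of adequately reported C-short items in published articles between the two groups".
- **Analysis of primary endpoint** keeps that target for the estimate: "The effect of the intervention will be estimated as the mean difference in the proportion of C-short items adequately reported between the study arms". **Data analysis** adds the interval: "For the primary and secondary outcomes, we will estimate the mean difference between the two groups and report them with respective 95% CI".
- **Analysis of primary endpoint** then makes the test conditional. First branch: "If the data on the primary outcome are normally distributed, groups will be compared using an unpaired Student’s t-test". Second branch: "If the data are not normally distributed, comparisons will be performed using a non-parametric equivalent test (ie, Wilcoxon-Mann-Whitney test".
- **Data analysis** says how the condition is judged: "Data distributions will be inspected visually (ie, by histograms) instead of performing formal statistical tests for normality". That section's reference to severe departures from normality concerns the choice of descriptive summary. No threshold is given for the choice of test, and nothing is said about whether the person looking at the histograms is blinded to arm.
- **Sample size** rests on the t-test alone: "Based on a two sided t-test, a sample size of 166 (83 per treatment arm) will have a power of 80" per cent.
- **Analysis of secondary endpoints** applies the same switch to continuous secondary outcomes.

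**The concern.** The target, the estimate, the interval and the sample size all concern a difference in means. Only the test can move away from it, and it moves on a subjective reading of the outcome data. The Wilcoxon-Mann-Whitney test asks whether a score from one arm tends to exceed a score from the other. That is not the same hypothesis as equal means when the arms differ in spread or shape, which is plausible for a score pressed against its maximum.

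At stake is the headline result. The report could show p<0.05 beside a 95% CI for the mean difference that includes zero, or the reverse, for one primary outcome and with no stated precedence. A test picked after seeing the data by an unstated criterion is also easy to challenge, whichever way the result falls.

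**Working it through.** **1. The plan's sample size.** Inputs from Sample size, second scenario: means 0.71 and 0.82, SD 0.25, two-sided 5%, power 80%.

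Normal approximation: n = 2(1.960 + 0.842)² × 0.25² / 0.11² = 81.1, so 82 per arm. The exact (noncentral t) calculation gives 82.05, so 83 per arm, with power 80.5% at 83. The stated 83 reproduces. The first scenario (0.56 vs 0.70, power 90%) gives 67.99, so 68, which also matches.

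**2. Can the outcome look normal?** Assessment of outcomes scores each item yes or no ("All items will be judged as either ‘yes’ meaning adequately reported, ‘no’ meaning not adequately reported or not reported at all"), with not-applicable reserved for sub-items. An article's score is therefore k/10: 11 values, bounded at 1. Distance from mean to ceiling, in SDs:

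| Scenario | Arm | (1 − mean)/SD | Share a normal curve puts above 100% |
|---|---|---|---|
| 2 | control | (1 − 0.71)/0.25 = 1.16 | 12.3% |
| 2 | intervention | (1 − 0.82)/0.25 = 0.72 | 23.6% |
| 1 | control | (1 − 0.56)/0.25 = 1.76 | 3.9% |
| 1 | intervention | (1 − 0.70)/0.25 = 1.20 | 11.5% |

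These figures need no assumption beyond the plan's means and SD. If the scores are taken as beta-binomial (an assumed shape) with these means and SD, skewness is −0.73 (control) and −1.47 (intervention) in scenario 2, with 20% and 48% of articles at 10/10. In scenario 1 it is −0.17 and −0.68. A reader of the histogram would probably call scenario 2 non-normal. Scenario 1 is less clear.

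**3. What Wilcoxon tests.** Its null value is P(Y>X) + ½P(Y=X) = 0.5. In the beta-binomial model with equal means of 0.71 and SDs 0.25 and 0.18, this quantity is 0.469. With equal means of 0.82 it is 0.438. The mean difference is zero in both cases, yet the quantity that Wilcoxon tests is not at its null.

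**4. How often the tests disagree under the planned means (0.71 vs 0.82, 83 per arm).** Simulated; the shape and the second SD are assumptions.

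| Model | SD control / intervention | t-test power | Wilcoxon power | Disagree on significance |
|---|---|---|---|---|
| Beta-binomial | 0.25 / 0.25 | 79% | 95% | 16% |
| Beta-binomial | 0.25 / 0.20 | 87–88% | 85–86% | about 5% |
| Item rates of Table 3, shared article effect | 0.25 / 0.21 | 87% | 89% | 6% |
| Same, smaller control SD | 0.22 / – | 93% | 93% | 3% |
| Beta-binomial | 0.18 / 0.18 | 97% | 99% | 2% |

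At beta-binomial SDs of 0.25 / 0.18 the order reverses: 90% for the t-test and 81% for Wilcoxon.

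**5. Rejection when the means are equal (83 per arm, beta-binomial).**

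| Mean | SDs | t-test | Wilcoxon |
|---|---|---|---|
| 0.71 | 0.25 / 0.25 | 4.8% | 4.8% |
| 0.71 | 0.25 / 0.23 | about 5% | 5–6% |
| 0.71 | 0.25 / 0.20 | about 5% | 8–9% |
| 0.71 | 0.25 / 0.18 | 4.9% | 10.8% |
| 0.82 | 0.25 / 0.25 | 5.4% | 5.1% |
| 0.82 | 0.25 / 0.18 | 5.1% | 29.9% |

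**6. Does the t-test need the fallback?** No. On this bounded, skewed score with 83 per arm it stays near 5% type I error in every row of step 5 and has 79% simulated power in the planning case (80.5% by formula). Student and Welch versions were practically identical.

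**The case against.** The branch is itself pre-specified, with both tests named, so this is an imprecise trigger and not a free choice after seeing p-values. The mean difference and its 95% CI are reported on either branch; only the p-value moves. Both points stand, and they limit the harm to a mismatch between p-value and interval.

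The large simulated effects also depend on assumptions. A beta-binomial treats the ten items as equally likely, and holding the SD at 0.25 with a mean of 0.82 forces 48% of articles to a perfect score. With the unequal item rates of Table 3 the tests have nearly equal power and disagree in 6% of trials or fewer. The high false-rejection rates need clearly different spreads at identical means, and no section predicts that. This stands too.

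Four stronger readings are tempting, and the documents do not support them:

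- **That the histogram is read unblinded.** The protocol does not say who looks, or whether arms are identified.
- **That the switch is certain.** No cut-off is given, and the case is weaker under the first scenario.
- **That the sample size is wrong.** It is right for the t-test, and no general loss of power under Wilcoxon is shown: the order of the two tests changes with the spread.
- **That the type I error is inflated.** With equal distributions both tests sit near 5%. Only if the test were chosen to suit the result would the beta-binomial figure rise, to 5.9% (both arms at 0.71) or 7.2% (both at 0.82), and nothing suggests that intent.

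What the objection does not remove is that the likely branch tests something other than the declared outcome, with no rule for a conflict.

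**Conclusion.** The concern holds as a should-fix. The protocol lets a visual judgement, with no stated criterion, decide the primary test. Under the scenario that fixes the sample size, the judgement will probably lead to a test of a different quantity from the one defined, estimated and used for sizing.

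The distance to the ceiling follows from the plan's own figures. The frequency of conflict does not: about 5% to 16% of trials under the planned means with a control SD of 0.25, and 2% to 3% in the cases with smaller SDs, all conditional on an assumed shape. With equal means Wilcoxon rejects in about 5% of trials when the spreads are similar, and in more when they differ. The estimate, its interval and the 83 per arm are unaffected.

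**What to change.** In Analysis of primary endpoint, replace the conditional rule with one statement: the primary p-value and the 95% CI both come from one pre-specified test of the difference in mean proportions, whatever the histogram shows. Either a Welch t-test or the Student's t-test used for sizing will do. List Wilcoxon-Mann-Whitney as a sensitivity analysis that does not decide the primary conclusion.

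In Analysis of secondary endpoints, remove the same switch and name the test for each continuous outcome in advance. Histograms can still guide the choice of descriptive summaries.

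The cost is wording only. The sample size stays at 83 per arm, with about 5% type I error and about 80% power under the planning assumptions. The change should be made before outcome data are examined. Whether to adjust for journal is a separate question that this fix does not need.
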